### Sample size

We aim to include 500 frail older patients (250 patients of intervention GP practices and 250 patients of control GP practices). We aim to optimize participation by means of personal home visits, however, we anticipate a drop-out rate of approximately 20% between T0 and T1 (e.g. due to death, refusal). Accordingly, we expect 400 patients at T1 in the intervention and control groups. Sample size calculations are based on the mean well-being score (SPF-IL) of a comparable Dutch population of frail community-dwelling older persons (N=945) [137]. To detect a mean improvement in well-being of 1/4 standard deviation (SD) based on the SPF-IL, we need at least 198 older patients in each group (based on a mean SPF-IL score of 2.56 [SD = 0.45]; alpha (two-sided) = 0.05, beta = 0.20, ratio 1:1).

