**Methods:**

The longitudinal evaluation study has a matched quasi-experimental design with one pretest and one posttest (12 month follow-up) and is conducted in the Netherlands between 2014 and 2017. Both quantitative and qualitative methods are used to evaluate effectiveness, processes, and cost-effectiveness. In total, 250 frail older persons (75 years and older) of 11 GP (general practitioner) practices that implemented the FFF approach are compared with 250 frail older patients of 4 GP practices providing care as usual. In addition, data are collected from healthcare professionals. Outcome measures are based on our theoretical model.

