### Statistical analyses

Descriptive statistics are used to describe the study population at the two time points in the evaluation study (baseline and 12 month follow-up). Baseline variables are compared to detect differences between patients and professionals in the intervention group (FFF approach) and control group (care as usual). To assess baseline differences between the groups we use unpaired Student’s t-tests (continuous variables with normal distributions), Mann-Whitney U-tests (continuous variables with non-normal distributions) and Chi-square tests (categorical variables). Effect analyses are performed based on the intention-to-treat principle. Analyses of outcomes are performed by means of univariate, multivariate, and multilevel methods (to account for the nested structure of the data). To analyze the differences in outcomes between the intervention group and control group, we employ linear mixed model with random effects (multilevel analysis). To estimate the effects of the FFF approach after 12 months a difference in differences model will be used followed by a sensitivity analysis method specifically developed for difference in differences model based on more general methods of bounds developed by Rosenbaum [138]. Potential confounding and effect modification is accounted for when performing the analyses and, if necessary, adjustments for baseline differences are made. To handle missing data multiple imputation techniques will be used. Ultimate goals of these analyses are to test the assumptions of the theoretical framework with the instruments described in the study protocol. Finally, we will assess clinical relevance of improvements made in cognitions and behaviors among both patients and professionals. The software package IBM SPSS statistics version 23 is used for all statistical analyses.

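### The 80% power claim for 1/4 SD rests on 198 independent patients per group: 198 fits only a one-sided alpha, and clustering in 11 and 4 practices is left out

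*Protocol article*

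**What the plan says.** The Sample size section gives all its inputs. The target is "To detect a mean improvement in well-being of 1/4 standard deviation (SD) based on the SPF-IL", "based on a mean SPF-IL score of 2.56 [SD = 0.45" and "alpha (two-sided) = 0.05, beta = 0.20, ratio 1:1". From these it concludes that "we need at least 198 older patients in each group". On recruitment it says "We aim to include 500 frail older patients (250 patients of intervention GP practices and 250 patients of control GP practices" and "we anticipate a drop-out rate of approximately 20% between T0 and T1", which leaves 400 patients at follow-up, or 200 per group. Drop-out is the only allowance made.

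The approach is delivered by practice. According to the abstract, patients of 11 FFF practices "are compared with 250 frail older patients of 4 GP practices providing care as usual". The Statistical analyses section recognises this and specifies "multilevel methods (to account for the nested structure of the data". It names a linear mixed model with random effects for the group comparison and a difference-in-differences model for the 12-month effect.

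**The concern.** The analysis section accepts that patients in one practice resemble each other; the sample size section does not. With whole practices in one arm or the other, part of the error comes from practices, and more patients per practice do not remove it. The control arm is the weak side: four practices supply all of its information.

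The number itself also has to be checked against its stated two-sided alpha. If 198 is already too few for independent patients, no clustering allowance can be hidden inside it.

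At stake is how the primary well-being result is read. If it is null, readers will take it as evidence from a study with 80% power against a 1/4 SD benefit. If the study never had that power, a null result says much less.

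**Working it through.** **Inputs.** From Sample size: d = 0.25 SD (0.25 × 0.45 = 0.1125 points), two-sided alpha 0.05, power 80%, ratio 1:1, 250 enrolled and 20% drop-out per group, so 250 × 0.8 = 200 analysed. From Setting and GP practices: 11 intervention and 4 control practices. Assumed, because the article does not give them: the ICC, equal practice sizes within each arm, and the correlation r between baseline and follow-up.

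**Step 1: the plan's own figure.** n per group = 2(z_alpha + z_power)² / d².
- Two-sided: 2 × (1.960 + 0.842)² / 0.0625 = 251.2, so 252.
- One-sided: 2 × (1.645 + 0.842)² / 0.0625 = 197.8, so 198.

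The published 198 is reproduced only with one-sided alpha 0.05. Dividing by 0.8 gives 248, in line with the 250 enrolled. So 198 contains drop-out afterwards and nothing for clustering.

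**Step 2: power with no clustering.** With 200 per group, SE = √(2/200) = 0.100 SD. Power = Φ(0.25/0.100 − 1.960) = Φ(0.54) = 70.5%. The effect detectable at 80% power is 2.802 × 0.100 = 0.28 SD.

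**Step 3: add clustering, follow-up scores.** Patients per practice: 200/11 = 18.2 and 200/4 = 50. Design effect DE = 1 + (m − 1) × ICC in each arm. SE = √(DE_int/200 + DE_ctl/200). Power = Φ(0.25/SE − 1.960).

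| ICC | DE intervention | DE control | SE (SD) | Power | Power, t on 13 df | Detectable effect (SD) |
|---|---|---|---|---|---|---|
| 0 | 1.00 | 1.00 | 0.100 | 70.5% | 64% | 0.28 |
| 0.01 | 1.17 | 1.49 | 0.115 | 58% | 52% | 0.32 |
| 0.02 | 1.34 | 1.98 | 0.129 | 49% | 44% | 0.36 |
| 0.05 | 1.86 | 3.45 | 0.163 | 34% | 30% | 0.46 |

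The 13 degrees of freedom are 15 practices minus 2. The SE ratios to the ICC 0 row are √1.331 = 1.15, √1.662 = 1.29 and √2.655 = 1.63.

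**Step 4: the planned contrast.** A change score has variance 2(1 − r) in units of SD². With r = 0.6 this is 0.8, so each squared SE in Step 3 is multiplied by 0.8, and the ICC is now that of change.

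| ICC of change | SE (SD) | Power |
|---|---|---|
| 0 | √0.00800 = 0.089 | 80% |
| 0.01 | √0.01065 = 0.103 | 68% |
| 0.02 | √0.01330 = 0.115 | 58% |
| 0.05 | √0.02124 = 0.146 | 40% |

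At r = 0.5 the variance is 1 and the Step 3 figures return; below 0.5 the change score does worse than those.

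**Step 5: the random terms.** In a pre-post contrast a stable practice effect is present at both times and subtracts out. A practice intercept alone therefore does not carry the variation that matters here, which is practices changing by different amounts. The article's Process evaluation section itself expects delivery and reception to differ between sites.

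**The case against.** The strongest reply is that Step 3 is not the planned estimator. A difference-in-differences removes stable practice differences, the ICC of change may be smaller than the ICC of level, and baseline information recovers precision. That is fair, and it is why Step 4 is shown. Under a baseline-adjusted comparison with r = 0.6 (variance × 0.64), power would be about 88% at ICC 0, 77% at 0.01, 68% at 0.02 and 48% at 0.05. But the Sample size section invokes no correlation, and even these figures fall below 80% from ICC 0.01 upward.

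Patient-level matching on sex, frailty score and education may lower between-practice variance somewhat. The Strengths and limitations section says that it is used instead of matching at practice level, so it cannot be counted on to remove practice effects. The equal practice sizes are an assumption, since no counts per practice are given.

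Three stronger readings are tempting and not supported:
- A reader might infer that clustering explains the whole shortfall. It does not: on follow-up scores at ICC 0.01, the fall from 80% to about 70% comes from sidedness and only the further fall to 58% from clustering.
- A reader might infer that the planned analysis will inflate the type I error. That would follow from an analysis that ignores variation between practices in change. The Statistical analyses section plans a mixed model and does not list its random terms, so the article does not show this.
- A reader might treat the missing random terms and degrees of freedom as an omission. A separate analysis plan commonly holds such details.

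**Conclusion.** The claim of 80% power at two-sided 0.05 for 1/4 SD is wrong as written. That 198 does not match its stated alpha needs no assumption: the two-sided requirement is 252, and 200 per group gives about 70%. That the calculation leaves out clustering which the analysis section recognises is equally plain from the text.

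The size of the clustering loss is conditional. Over assumed ICCs of 0.01 to 0.05, power runs from about 58% to 34% for follow-up scores, and from about 68% to 40% for change scores with r = 0.6. These are ranges under stated assumptions, not the known power of the study.

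**What to change.** Keep the recruited numbers. In the Sample size section:
- Correct the sidedness: either state 252 per group for two-sided alpha, or say openly that 198 corresponds to one-sided 0.05.
- Replace the single 80% claim with power, or the detectable difference, over a stated ICC range such as 0.01 to 0.05. Base it on 11 and 4 practices with their actual counts and on the difference-in-differences estimator, and state the baseline correlation assumed.

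As a secondary point, wherever the model is specified in full, let change vary between practices (a random practice-by-time effect) and use small-sample degrees of freedom such as Satterthwaite or Kenward-Roger for the group-by-time contrast.

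The cost is wording and model specification, with no extra patients. The downside is real: the stated power falls. If practices change differently, intervals widen materially, with a standard error about 15% to 63% larger over ICC 0.01 to 0.05 than in an analysis that ignores practice, and more again with few degrees of freedom.

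### The 198 patients per group do not follow from the stated two-sided inputs, which require 252; with 200 per group at T1 the simple comparison has about 70% power, not 80%

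*Protocol article*

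**What the plan says.** The Sample size section of the protocol article gives a full set of inputs and a result.

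- Target difference: "To detect a mean improvement in well-being of 1/4 standard deviation (SD) based on the SPF-IL".
- Variability: "based on a mean SPF-IL score of 2.56 [SD = 0.45", taken from a comparable Dutch frail population.
- Error rates and allocation: "alpha (two-sided) = 0.05, beta = 0.20, ratio 1:1".
- Result: "we need at least 198 older patients in each group".
- Attrition: "we anticipate a drop-out rate of approximately 20% between T0 and T1".
- Recruitment: "We aim to include 500 frail older patients (250 patients of intervention GP practices and 250 patients of control GP practices"). From this, "we expect 400 patients at T1 in the intervention and control groups", that is 200 per group.

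The section mentions no pre-post correlation, no within-pair correlation from the matching and no design effect. The Statistical analyses section plans a linear mixed model with random effects and a difference-in-differences estimate of the 12-month effect, with adjustment for baseline differences if necessary. The SPF-IL is the primary outcome.

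**The concern.** A reader who enters the printed inputs into the standard two-sample formula does not get 198. The printed alpha and the printed sample size do not belong together, and the gap is too large for rounding to explain.

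This is the article's only power statement for the primary outcome. The recruitment target appears to be built on it: 198 / 0.8 = 247.5, close to the planned 250 per group. If the statement is wrong, a null result on the SPF-IL would be read as coming from a study with a 20% chance of missing a quarter-SD effect, when under the printed inputs that chance is nearer 30%. The Background already describes inconsistent results from evaluations of such approaches, so how a null result is read matters here.

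**Working it through.** **Inputs (Sample size section).** SD = 0.45; difference = 0.25 × 0.45 = 0.1125 points, so d = 0.25; beta = 0.20, so z = 0.842; ratio 1:1; two-sided alpha 0.05, so z = 1.960.

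**Step 1: the required size as declared.** For two means with equal groups, n per group = 2(z_alpha + z_beta)² / d².

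- Two-sided 0.05: 2 × (1.960 + 0.842)² / 0.25² = 251.2, so 252 per group. The t-based answer is also about 252.

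The stated 198 is not reproduced.

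**Step 2: what does reproduce 198.**

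- One-sided 0.05: 2 × (1.645 + 0.842)² / 0.25² = 197.8, so 198. The t-based version gives 198.5, so the match is exact only for the normal approximation.
- Rounding the difference does not rescue the two-sided reading: 0.11 points gives 263, 0.113 gives 249, 0.12 gives 221 and 0.13 gives 189.

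**Step 3: power at the planned size.** Two-sided 0.05, d = 0.25, independent patients, noncentral t:

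| Per group | Power |
|---|---|
| 198 | 69.9% |
| 200 (expected at T1) | 70.3% |
| 250 (no drop-out) | 79.7% |

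**Step 4: detectable difference at 200 per group with 80% power.** (1.960 + 0.842) × √(2/200) = 0.280 SD, and 0.280 × 0.45 = 0.126 points, against the stated 0.25 SD (0.1125 points).

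**Step 5: what 80% power for 0.25 SD would take.** 252 / 0.8 = 315 recruited per group, against the planned 250.

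**Step 6: what the baseline measurement could change.** The article states no correlation, so r below is an assumption. For a two-wave difference in differences with equal SDs, the variance of a change is 2(1 − r)SD², so the effective d is 0.25 / √(2(1 − r)). At 200 per group:

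| Assumed r | Difference in differences | ANCOVA |
|---|---|---|
| 0.4 | 62% | not computed |
| 0.5 | 70% | 82% |
| about 0.61 | 80% | not computed |

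At r = 0.5, 2(1 − r) = 1, so the change score is exactly as variable as a single score and nothing is gained. The 82% uses the ANCOVA variance (1 − r²)SD² and does not carry over to difference in differences.

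**The case against.** The strongest reply is that 198 may come from a different calculation that the article condensed. Three unstated assumptions would bring a two-sided answer close to 198:

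- a pre-post correlation of about 0.46 under ANCOVA (251.2 × (1 − 0.46²) ≈ 198);
- a pre-post correlation of about 0.61 for change scores (251.2 × 2 × (1 − 0.606) ≈ 198);
- a within-pair correlation of about 0.21, given the one-to-one matching (251.2 × (1 − 0.21) ≈ 198).

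This has some force against a claim about where the figure came from. A reader might infer that the investigators ran, or intend, a one-sided test. The article supports neither: it declares a two-sided alpha, and a one-sided calculation is only inferred from the match. The reply does not repair the paragraph. None of these correlations is stated, and the figure is explicitly tied to the mean and SD of the score. Condensation does not help either, because the article prints a complete set of inputs and a result that does not follow from them.

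A second reply is that 70% is not the power of the planned analysis. That is correct. It describes the simple unadjusted comparison implied by the Sample size section. A pre-post correlation above 0.5 would raise power under difference in differences, and a lower one would reduce it. Clustering would also reduce it. The article gives no intraclass correlation. As an assumption only, values of 0.01 and 0.02, with equal-sized practices within each arm (11 and 4) and 200 per group, give about 58% and 49% for the unadjusted comparison. So 70% is neither a worst case nor a final figure.

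A third reply is that the 400 are patients expected at T1, not the analysed set: intention-to-treat analysis with multiple imputation may include all 500. Imputing missing T1 outcomes restores little information about the effect, so about 70% remains a fair approximation.

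**Conclusion.** The point stands as a mismatch between printed inputs and printed result. Two-sided alpha 0.05, beta 0.20, a quarter SD and 1:1 allocation require 252 per group, not 198. At 200 per group the simple two-group comparison has about 70% power for 0.25 SD, and 80% power for 0.28 SD (0.126 points). These figures assume independent patients, an SD of 0.45 and no credit for baseline or matching.

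Two stronger conclusions are tempting but not supported. The one-sided origin of 198 is a strong inference from an exact match, not something the document says. Nor does it follow that the study must recruit 315 per group: that is one way to reconcile the paragraph, and stating the power correctly at the planned size is another. The error must be corrected because it concerns the only stated power for the primary outcome.

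**What to change.** Keep 500 patients and the two-sided alpha, and restate the Sample size paragraph along these lines:

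> With about 200 patients per group at T1 the study has about 70% power (two-sided alpha 0.05) for a difference of 0.25 SD, or 80% power for 0.28 SD (0.126 points), before allowance for clustering by GP practice.

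If credit is wanted for the baseline measurement or the matching, state and justify the assumed correlation and compute power for the planned difference-in-differences estimator. An ANCOVA figure should be quoted only if ANCOVA becomes the planned analysis. Do not move to a one-sided test to make 198 fit.

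The cost is the rewording of one paragraph and a less favourable stated power. No extra patients are needed.

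### The 198 per group and 80% power are not those of the planned difference in differences, because the T0-T1 correlation is not given, and 198 does not match the stated two-sided test

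*Protocol article*

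**What the plan says.** The Sample size section of the protocol article gives a full calculation.

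- Target: "To detect a mean improvement in well-being of 1/4 standard deviation (SD) based on the SPF-IL".
- Source of the spread: "Sample size calculations are based on the mean well-being score (SPF-IL) of a comparable Dutch population of frail community-dwelling older persons (N=945", with the calculation "based on a mean SPF-IL score of 2.56 [SD = 0.45". This is the SD of a score and is not described as the SD of a change.
- Error rates and allocation: "alpha (two-sided) = 0.05, beta = 0.20, ratio 1:1".
- Result: "we need at least 198 older patients in each group".
- Attrition: "we anticipate a drop-out rate of approximately 20% between T0 and T1", from 250 recruited per group; hence "we expect 400 patients at T1 in the intervention and control groups", which is 200 per group.

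The Statistical analyses section then names the effect estimator: "To estimate the effects of the FFF approach after 12 months a difference in differences model will be used". It also plans a multilevel linear mixed model, with adjustment for baseline differences where needed. Neither section gives a correlation between the two SPF-IL measurements or an SD of change.

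**The concern.** A sample size calculation should use the variance of the estimator that will be tested. The SD of a single score fits a comparison of two group means at one time point. A difference in differences compares mean changes, so its variance depends on how strongly a patient's two scores correlate over 12 months. Without that correlation, a reader cannot tell what power the planned analysis has.

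The stated figure also has to follow from its own inputs, and here it does not. If the true power is below 80%, a null result on well-being may be read as stronger evidence of no effect than it is. If it is above 80%, the article undersells the study.

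**Working it through.** **Inputs from the Sample size section:** SD 0.45; effect 0.25 x 0.45 = 0.1125 points; alpha 0.05 two-sided; power 80%; ratio 1:1; 200 completers per group.

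**Assumptions:** rho is not in the document and is shown as a range. The SD is taken as 0.45 at both times. Patients are treated as independent.

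**1. The plan's own figure.** For two means at one time point, n per group = 2(z_alpha + z_beta)^2 / 0.25^2.

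- Two-sided: 2(1.960 + 0.842)^2 / 0.0625 = 251.2, so 252.
- One-sided: 2(1.645 + 0.842)^2 / 0.0625 = 197.8, so 198.

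The stated 198 is therefore the one-sided answer. Two-sided power with 198 per group is Phi(0.25 x sqrt(198/2) - 1.960) = 70.1%; with 200 per group it is 70.5%.

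**2. The planned estimator.** SD of change = 0.45 x sqrt(2(1 - rho)), so:

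- n per group = 251.2 x 2(1 - rho)
- power = Phi(0.25 / sqrt(2(1 - rho)) x sqrt(n/2) - 1.960)
- detectable effect in SD units at 80% power = (1.960 + 0.842) x sqrt(2/n) x sqrt(2(1 - rho))

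| rho | 2(1 - rho) | n per group for 80%, two-sided | Power, 200 per group | Detectable effect, 200 per group |
|---|---|---|---|---|
| 0.3 | 1.4 | 352 | 56% | 0.33 SD |
| 0.4 | 1.2 | 302 | 63% | 0.31 SD |
| 0.5 | 1.0 | 252 | 71% | 0.28 SD |
| 0.6 | 0.8 | 201 | 80% | 0.25 SD |
| 0.7 | 0.6 | 151 | 90% | 0.22 SD |

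**3. Separating the two effects.** The factor 2(1 - rho) equals 1 at rho 0.5, so at that value the choice of SD costs nothing, and the whole shortfall from 80% to 71% comes from sidedness. With the correct two-sided 252 per group, the same power formula gives about 73% at rho 0.4, 80% at 0.5 and 88% at 0.6. That spread around 80% is what the SD mismatch contributes alone.

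**4. Both together.** 198 per group gives 80% two-sided power for the difference in differences when 251.16 x 2(1 - rho) = 198, that is, rho = 1 - 198/(2 x 251.16) = 0.606, or about 0.61.

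**The case against.** The strongest objection is that no harm of known direction is shown. Above rho 0.5 a single-score SD is conservative for a difference in differences, and nothing in the document suggests that rho is below 0.5. This stands. A reader might infer that the study is underpowered because of the difference in differences; the document does not support that, since the result depends on a correlation it does not give.

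A reader might also infer that 80% power with 198 per group is right for a post-test comparison and fails only for the difference in differences. That is not so: at the stated two-sided alpha, the post-test comparison has about 70%. Nor can the 0.61 threshold be charged to the SD alone, as step 3 shows. Conversely, rho of about 0.6 would bring the required number close to 198, but the article states no such value, so this cannot be taken as its derivation.

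A further objection is that adjusting for baseline SPF-IL would change the factor to 1 - rho^2, which never exceeds 1; 198 per group would then suffice two-sided from rho = sqrt(1 - 198/251.16) = 0.46. This softens the point. However, the article names difference in differences for the 12-month effect and makes baseline adjustment conditional, and the power would still depend on rho.

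Last, a journal article condenses, and a correlation could sit in the full protocol. That would excuse silence. Here the article prints a complete calculation whose inputs do not give its result two-sided and whose variance is not that of the estimator it names.

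**Conclusion.** The point holds in a limited form. The stated 198 per group and 80% power are not those of the planned difference in differences. The SD mismatch taken alone has no known direction. What can be shown without any outside figure is that the stated inputs need 252 per group, not 198, and that 198 has about 70% two-sided power for a comparison at one time point.

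Taken together, power with 200 completers per group runs from about 63% to 90% over assumed rho 0.4 to 0.7. The figures rest on equal SDs of 0.45 at both times and independent patients. Any positive clustering of change within the 15 practices would lower them. This is a correction to a stated property of the study, not evidence that the design fails.

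**What to change.** In the Sample size section:

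- Correct the two-sided figure: 252 per group for a single-time comparison, or about 70% power at 198.
- Restate the power for the difference in differences at the expected 200 completers per group, using SD of change = 0.45 x sqrt(2(1 - rho)). Declare rho as an assumption, taken from longitudinal SPF-IL data if available and otherwise shown over 0.4 to 0.7.
- Give the detectable effect beside each power, and say that the power may be lower or higher than 80% and that clustering is ignored in these figures.

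The cost is one recalculation and a few sentences. No extra patients and no change of analysis are needed. The downside is a stated power that may look less favourable.
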